### Data management {19}

All data will be systematically recorded in an electronic database. Participants will be identified solely by a unique study identification number to maintain pseudonymization, and no personally identifiable details will be stored in the database. To ensure data quality, various strategies will be employed, including meticulous recruitment, a structured and time-limited protocol, a run-in period, minimized participant burden, and the establishment of a trusting relationship between research units and participants. Additionally, double data entry will be implemented. Biological samples will be stored under optimal conditions following standard procedures. Blood samples will be aliquoted and preserved at − 20 °C for up to 5 years, with proper documentation of their usage or destruction. Preserved samples will be exclusively utilized for research purposes with the donor’s consent. Destruction of samples will be properly documented. The data will be made available upon request after publication.

### Confidentiality {27}

Identifiable details will be safeguarded through the allocation of unique study identification numbers, ensuring anonymity in data storage and analysis. Hard copies linking participant identification numbers to contact details will be stored in a locked file cabinet within a secure office. Access to this information will be restricted to key members of the research team. Participant files, source data, and related study documents will be retained for 5 years, the maximum duration allowed by the institution.

### Plans for collection, laboratory evaluation, and storage of biological specimens for genetic or molecular analysis in this trial/future use {33}

Blood, fecal (four or five scoops totaling 4 g), and urine samples will be collected at the beginning and end of each intervention phase.

#### Analysis of biochemical parameters, adipokines, and inflammatory markers (RU1, RU2, and RU3)

Blood samples will be centrifuged at 3000 rpm for 15 min to obtain serum and plasma. Samples will be aliquoted and stored at − 20 °C until analysis. Biochemical parameters (complete blood count with formula, lipid and glycemic profiles, vitamin and mineral profile) will be evaluated in all participants according to standardized routine laboratory protocols. Fasting insulin secretion capacity will be evaluated as the Homeostatic Model Assessment for Insulin Resistance (HOMA-IR) according to the related equation. Fasting plasma concentrations of ghrelin, leptin, adiponectin, resistin, visfatin, and plasminogen activator inhibitor 1 (PAI-1) will be measured using commercial enzyme-linked immunosorbent assay kits, according to the manufacturer’s instructions. Pro-(anti)-inflammatory cytokines (e.g., interleukin (IL)-1ra, IL-4, IL-10, interferon-gamma (IFN-γ), tumor necrosis factor-alpha (TNFα)) will be analyzed in plasma according to manufacturers’ instructions.

#### Analysis of oxidative stress to macromolecules (RU1, RU3)

The 5-, 8-, 12-, and 15-F2-isoprostanes will be detected and quantified in urine samples through a high-performance liquid chromatography-tandem mass spectrometry (HPLC–MS/MS) method [23]. Protein and additional markers of lipid damage (e.g., oxidized LDL) will be investigated through analysis of protein carbonyls in serum samples by using specific enzyme-linked immunosorbent assay (ELISA) assays. The evaluation of deoxyribonucleic acid (DNA) damage will employ the Comet assay, specifically focusing on hydrogen peroxide (H2O2)-induced DNA strand breaks and endogenous oxidized DNA bases, providing insights into oxidative stress [24].

#### Analysis of markers of endothelial and intestinal permeability (RU1)

Endothelial permeability will be measured through the analysis in serum samples of several markers (e.g., VE-cadherin, occludin (OCLN), and claudin-5 (CLDN-5)), while intestinal permeability will be assessed by measuring zonulin, calprotectin, and tight junction proteins in serum and fecal samples. Analysis will be performed by using ELISA assays.

#### Analysis of fecal microbiota profiles and SCFAs (RU2)

Fecal sample collection kits, including containers, will be provided to each participant. Fecal microbiota profiles and SCFAs (acetic, butyric, isobutyric, propionic, valeric, and isovaleric acids) will be evaluated. Total microbial DNA will be extracted from the faces by repeated scouring. The V3 and V4 hypervariable regions of the 16S rRNA gene for bacteria and ITS1-4 for fungi will be sequenced on the Illumina MiSeq platform, following the Illumina protocol for preparing 16S metagenomic sequencing libraries. SCFAs will be extracted using aqueous sodium hydroxide (NaOH) containing an internal standard. After extraction, an aliquot of supernatant fecal water will be derivatized with a propanol/pyridine mixture. The organic extract will be analyzed by gas chromatography-mass spectrometry (GC–MS) using deuterated internal standards and an appropriate GC Wax column.

#### Analysis of fatty acid composition of red blood cell phospholipids (RU1)

From the tube containing plasma, the buffy layer of white blood cells will be removed using a pipette. Red blood cells (RBCs) will be washed twice in an equal volume of a physiologic solution (0.9% NaCl, w/v). Two aliquots (0.5 mL) of RBCs will be stored at − 80 °C until the analysis. Extraction of RBC phospholipids will be carried out in accordance with the method previously described by Simonetti et al. [25]. The FA composition of RBCs will be obtained by GC analysis following the method described by Ackman [26].

#### Measurement of food waste and metabolic food waste (RU1, RU3)

Food waste will be monitored by a specific food diary [27]. Subjects will be asked to fill a 3-day weighed food waste diary for each intervention arm, by registering type and weighed amount of waste. Waste will be quantified not only as a net amount of food waste (grams per week of total waste and for each food group) but also performing a nutritional and environmental assessment of food wasted [28].

The Metabolic Food Waste indicator [MFW (kg of food)] corresponds to the amount of food leading to an excess of body fat and its impact on the environment expressed as carbon [MFW (kgCO2 eq)], water [MFW(× 10 L)], and land footprint [MFW(× 10 m^2^)] [29]. Calculations will be applied in agreement with our previous publication [29] with few modifications, including data from new databases recently developed [28]. Briefly, the dietary intakes of volunteers will be analyzed and aggregated based on similar macronutrient composition. Then, the energy contribution of each food/food category to the daily energy intake will be calculated. Fruits and vegetables will be excluded because they are low energy dense foods not contributing to obesity. Then, anthropometric measurements relative to body fat mass will be considered. The difference between individual and average body fat mass will be multiplied for energy content of 1 kg of body fat to reach the total energy from exceeding body fat and distributed among the different foods according to their percentage contribution to total energy intake. The acquired data will allow us to calculate the carbon, water, and land footprints.

#### Calculation of the inflammatory index of foods (RU3)

The pro-(anti)-inflammatory effect of the tested food samples will be assessed after a simulated in vitro human digestion and, consequently, their exposure in a human culture cell-based in vitro model will be assessed, with the production of a small database of results for NII development. Aliquots of pairs of foods belonging to the same food group but of different NOVA categories (e.g., NOVA 1 versus NOVA 4) will be processed, i.e., washing, cleaning, cutting, mincing, and undergo cooking procedures, to be used for a human simulated in vitro digestion process, following the protocol by Minekus et al. [30]. In detail, time-dependent subsequent oral, gastric, and intestinal phases of digestion will be applied by mixing foods with solutions of digestive enzymes and buffer solutions for the digestion of carbohydrates, lipids, and proteins. Digested samples obtained during the time will be aliquoted and stored at − 20 °C till analysis.

Concerning the anti-(pro)-inflammatory effects of such digested foods, the digested samples will be incubated with innate immune cells (THP-1). Three concentrations of digesta will be used based on preliminary experiments, to identify a dose response effect, assessing the inflammatory response in the supernatants by ELISA assays after 24 h [31]. The inflammatory response will be measured in terms of 4 pro-inflammatory and anti-inflammatory factors’ production, such as inflammatory chemokines (IL-8), inflammatory cytokines (TNFα), and anti-inflammatory cytokines (IL-10, transforming growth factor-β (TGF-β)) [31]. The inflammatory response of the THP-1 to digested food samples will be compared to the response to a prototypical inflammatory stimulus (i.e., lipopolysaccharides (LPS)), used as reference control. To define the pro or anti-inflammatory unbiased effects due to digested samples and not to endotoxin contamination, the amount of endotoxin (e.g., LPS) in the digested samples will be evaluated by the chromogenic Limulus amoebocyte lysate assay [32, 33].

## Statistical methods

### Statistical methods for primary and secondary outcomes {20a}

Statistical analyses will be performed using SPSS software for Macintosh (SPSS Inc., Chicago, IL, USA). A *P* value < 0.05 will be considered statistically significant. Data will be analyzed using intention-to-treat and on-treat procedures. The primary outcome (change in body weight) will be analyzed within each group using Student’s *t*-test for paired data. The difference in absolute change (mean value at baseline subtracted from the mean value after the intervention for each subject) will be estimated using the Student’s *t*-test for independent data. Evaluation of distributions and checking for outliers will be performed using histograms and box plots. If appropriate, variables will be logarithmized to normalize the distributions of data. Continuous variables that follow a normal distribution will be summarized using the mean and standard deviations. Categorical variables will be presented in terms of frequencies and percentages. After testing the regression assumption, a general linear model for repeated measurements with adjustments for possible confounding factors will be run to compare the effects of different interventions. Data for the general linear model will be reported as geometric means and 95% confidence intervals. The same analyses will be performed for secondary outcomes. Microbial alpha (richness, Simpson’s, Gini-Simpson’s, inverse Simpson and Shannon’s indices, evenness and dominance) and beta (weighted UniFrac and Bray–Curtis dissimilarity) diversity measures will be assessed using QIIME (v. 1.9).

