**Methods:**

Fifty clinically healthy individuals showing overweight and presenting a low-to-moderate cardiovascular risk profile will be recruited for a 7-month randomized, open, cross-over dietary trial. Eligible participants will be randomly assigned to a 3-month high-UPF MD (intervention group) or a low-UPF MD (control group), with a 1-month wash-out period. Both intervention diets will have identical food group compositions, with the intervention group consuming 5 servings/day of selected UPF items, and the control group consuming raw/minimally processed items from the same food group. Blood, urine, and fecal samples, alongside food/lifestyle diaries, will be collected from each participant before and after the dietary interventions. The primary endpoint will be the change in plasma LDL-cholesterol levels from baseline. Additional markers include blood pressure, anthropometric parameters, chemical parameters, glucose and lipid-related metabolic markers, incretins, inflammatory and oxidative stress markers, fecal microbiota composition, and short-chain fatty acids. Finally, food waste production will be evaluated through specific validated food diaries. The study has been approved by the Ethical Committee of the University of Milan and the Tuscany Regional Ethics Committee of the Azienda Ospedaliera Universitaria (AOU) - Careggi, Florence.

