### Outcomes {12}

The primary endpoint will be the change in LDL-cholesterol levels from baseline. Key secondary endpoints will include changes in total cholesterol and glycemic profile, circulating levels of adipokines, inflammatory markers, oxidative stress, markers of endothelial and intestinal permeability, microbiota composition, and short-chain fatty acids (SCFAs) values after 3-month dietary intervention vs. baseline. Additionally, the study will investigate the impact of interventions on environmental constraints, such as food waste and metabolic food waste. LDL-cholesterol will be measured as a unique and established quantitative primary outcome, while the assessment of anthropometric parameters, body composition, biochemical profile, SCFAs, and gut microbiota will provide information on the cardiometabolic status of participants. The metric used for analysis will be the change in mean values from the beginning to the end of each 3-month dietary intervention.

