### Sample size {14}

Sample size calculation is based on the results of a previously published study evaluating the impact of a MD intervention on human health [19]. To detect a 10% change in LDL-cholesterol levels with a statistical power of 90% (beta) and alpha set at 0.05, a randomization of 38 subjects (≥ 19 subjects in each group) is considered necessary. Considering possible dropouts, the number of participants was increased to 25 per group. Dropouts will be incorporated into the intention-to-treat analysis, including all participants initially randomized. In addition, per-protocol analysis will be conducted, focusing on those who successfully complete the study without major deviations.

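### The statistical methods section names change in body weight as the primary outcome; the abstract, the outcomes section and the sample size all use LDL-cholesterol

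*Protocol article*

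**What the plan says.** Three places in the protocol article identify LDL-cholesterol as the endpoint on which the trial is judged.

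- Abstract, Methods: "The primary endpoint will be the change in plasma LDL-cholesterol levels from baseline".
- Outcomes {12}: "The primary endpoint will be the change in LDL-cholesterol levels from baseline". The same section adds: "LDL-cholesterol will be measured as a unique and established quantitative primary outcome". It gives anthropometric measures a supporting role, and body weight is not among the key secondary endpoints it lists.
- Sample size {14}: "To detect a 10% change in LDL-cholesterol levels with a statistical power of 90% (beta) and alpha set at 0.05", giving 38 participants (at least 19 per group), raised to 25 per group for dropout.

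Statistical methods {20a} says otherwise: "The primary outcome (change in body weight) will be analyzed within each group". The procedures that follow are a paired t-test within group, an independent-samples t-test on the difference in change, and a repeated-measures general linear model. Secondary outcomes are to be handled in the same way, all at P < 0.05.

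**The concern.** The section that assigns the primary analysis names a different endpoint from the sections that define it and size the trial for it. This is not detail left to a separate analysis plan. The protocol makes two incompatible statements, and an analysis plan could adopt either one and claim to follow it.

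Two things are at stake. The first is the confirmatory status of LDL-cholesterol. Under section {20a} as written it becomes a secondary outcome, and the confirmatory claim moves to an endpoint with no sizing rationale. The second is error control. With two candidate primaries and no ordering between them, whichever gives the smaller P value could be reported as pre-specified.

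**Working it through.** **Step 1. The statements side by side**

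| Section | Primary endpoint or sizing basis |
|---|---|
| Abstract, Methods | Change in plasma LDL-cholesterol |
| Outcomes {12} | Change in LDL-cholesterol, described as unique |
| Sample size {14} | 10% change in LDL-cholesterol |
| Statistical methods {20a} | Change in body weight |

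Body weight appears again in the Discussion, but only in a list of outcome measures and not as primary. No sentence reconciles the fourth row with the other three.

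**Step 2. What the sample size supports**

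Inputs from Sample size {14}: 19 per group, power 90%, alpha 0.05. Sidedness is not stated; two-sided is assumed here. The document gives neither an SD nor a baseline LDL-cholesterol mean, so 38 can be neither reproduced nor refuted. Solving backwards for the standardized effect gives:

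- Two independent groups: d = (1.960 + 1.282) × √(2/19) = 1.05.
- Paired analysis of all 38 in the cross-over: d = (1.960 + 1.282) / √38 = 0.53.

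For an assumed baseline LDL-cholesterol of 115, 130 or 145 mg/dL, a 10% change is 11.5, 13.0 or 14.5 mg/dL. The SD implied by 38 is that change divided by d:

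- Independent groups: 10.9, 12.4 or 13.8 mg/dL.
- Paired (SD of the within-person difference): 21.9, 24.7 or 27.6 mg/dL.

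All of this concerns LDL-cholesterol. No corresponding calculation is possible for body weight, because the document gives no target difference and no SD for it.

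**Step 3. Illustration for body weight**

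The SDs here are assumptions, not document figures. The difference detectable with 90% power is d × SD:

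- Independent groups, 19 each, SD of change 2 to 5 kg: 1.05 × 2 = 2.1 kg to 1.05 × 5 = 5.3 kg.
- Paired, 38 participants, SD of the within-person difference 2 to 5 kg: 0.526 × 2 = 1.1 kg to 0.526 × 5 = 2.6 kg.

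This does not show that power for body weight is inadequate. It shows that the answer depends wholly on quantities the protocol does not state.

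**Step 4. False-positive risk with two candidate primaries**

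If success on either endpoint at 0.05 could be presented as the primary result:

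- Independent tests: 1 − 0.95² = 1 − 0.9025 = 0.0975.
- Any dependence: at most 0.05 + 0.05 = 0.10.
- Positively correlated tests: below 9.75%, falling to 5% only if the two tests always agree.

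Both changes are measured in the same people and the document gives no correlation, so 9.75% is illustrative.

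**The case against.** The strongest reply is that this is a stray bracket. A reader of the whole document would settle on LDL-cholesterol. The tests would be the same either way, since secondary outcomes receive the same analyses, so what is lost is a label. Analysts are also to be blinded to allocation, and the registration predates the start of recruitment and may name a single primary.

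Much of this is fair. The bracket probably is a slip, and LDL-cholesterol would not go unanalysed. But the label decides which result carries the confirmatory claim, and it is wrong in the section an analyst works from. Blinding to allocation does not fix which endpoint is primary. What the registration names is not in the documents at hand, so it cannot be relied on in either direction.

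A further argument against body weight is that both diets are prescribed as isocaloric, so little weight difference should be expected. That is an inference from the design, and a contestable one. Participants buy and prepare their own food, and the Background cites weight gain on ultra-processed food in the earlier trial. The finding does not depend on it.

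**Conclusion.** The concern holds. Statistical methods {20a} contradicts the abstract, Outcomes {12} and Sample size {14} on the identity of the primary outcome, and the document does not resolve it. As written, the primary analysis is attached to an endpoint with no stated effect size, SD or power, and the endpoint the trial was sized for is left as secondary.

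The conclusion rests on the text and needs no assumption. The 9.75% is a secondary illustration: it assumes independent tests and that either endpoint might be claimed, which the protocol does not say but does not exclude. An ambiguous primary endpoint undermines any confirmatory claim, so this must be corrected before outcome data are analysed.

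**What to change.** In Statistical methods {20a}, replace the bracketed reference to body weight with change in LDL-cholesterol. Keep the word change, to match the abstract and Outcomes {12}. State that this is the single primary outcome, tested at 0.05, and say whether the test is two-sided, which the document does not do at present. List body weight among the secondary outcomes.

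The corrected sentence would still attach the primary outcome first to a within-group paired test, so the same edit should say that the confirmatory comparison is the one between diets.

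If the investigators did intend body weight as primary, the abstract, Outcomes {12} and Sample size {14} would all have to change, with a justification and a sample size calculation for body weight.

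The cost of the LDL-cholesterol correction is a short text amendment through the Ethics Committee route the protocol already describes, made before outcome data are analysed. The sample size stays at 38, raised to 50, and no additional data are needed.

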## Trial design {8}

A 7-month randomized, cross-over, two-arm, open-label, superiority trial with a 1:1 allocation ratio to either intervention or control arms will be conducted, adhering to the SPIRIT reporting guidelines (see Fig. 1 and Supplementary file 1). In the development of the study protocol, there was no direct involvement from the public or patients. Despite the acknowledged significance of patient and public engagement in research, the protocol for this study was formulated within the framework of scientific and clinical expertise.

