### Participant timeline {13}

The study timeline is depicted in Fig. 2. Before starting the intervention, a 2-week run-in period will be implemented during which participants will be asked to complete a 3-day dietary record. Subsequently, participants will be randomly allocated into two groups: one assigned to the intervention arm and the other to the control arm. There will be four clinical evaluations of the study population: at the beginning (time 0) and at month 3 (T1) of the first dietary intervention, and at month 4 (T2) and month 7 (T3) of the second dietary intervention. At each time point, assessments of anthropometric measurements, body composition, and blood pressure will be made, and blood, stool, and urine samples will be collected.

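### The two diets' LDL changes are compared with an independent-samples t-test although the same participants supply both; no valid within-participant analysis is named as primary

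*Protocol article*

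**What the plan says.** The Trial design section describes "A 7-month randomized, cross-over, two-arm, open-label, superiority trial with a 1:1 allocation ratio". The abstract adds that the two 3-month diets come "with a 1-month wash-out period". The Participant timeline section places the four visits "at the beginning (time 0) and at month 3 (T1) of the first dietary intervention, and at month 4 (T2) and month 7 (T3"). The Outcomes section fixes the measure: "The metric used for analysis will be the change in mean values from the beginning to the end of each 3-month dietary intervention". Each participant therefore has two changes, T0 to T1 and T2 to T3, one on each diet.

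The section on statistical methods for primary and secondary outcomes then gives three analyses:

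- The primary outcome "will be analyzed within each group using Student’s *t*-test for paired data".
- The difference in absolute change, defined for each subject as the value after the intervention minus baseline, "will be estimated using the Student’s *t*-test for independent data".
- A general linear model for repeated measurements, adjusted for unnamed possible confounders, is to compare the interventions. Its results are to be given with 95% confidence intervals.

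The same analyses are to be used for the secondary outcomes. The section does not say which analysis decides the primary comparison.

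**The concern.** An independent-samples t-test assumes that the two sets of values come from unrelated people. Here they come from the same people, so its standard error leaves out the covariance between a person's two changes. The resulting p-value can be too large or too small, depending on the sign of that covariance. If it is too large, the trial gives up the within-person comparison that is the main reason for a cross-over of this size. If it is too small, a diet difference may be declared too readily.

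The paired tests within each diet ask whether the outcome moved while people ate a Mediterranean diet, which both arms do. The stated objective is whether including ultra-processed food makes a difference. A significant change on one diet and a non-significant one on the other does not answer that.

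Because the plan sets no order among the three analyses, the primary conclusion could rest on the invalid test or be chosen after the results are seen.

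**Working it through.** **Inputs.** From the protocol article: two-period cross-over; visits at months 0, 3, 4 and 7; the change over each diet as the metric; alpha 0.05 (sidedness not stated, two-sided assumed); power 90%; 38 participants required, 50 randomized. Not given: the SD of LDL change, the mean LDL, and the correlation *r* between a person's two changes. Those are assumed below and shown as ranges.

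**The plan's own figure.** The 38 can be neither reproduced nor refuted without an SD. Solved backwards with z-values 1.96 and 1.2816 (sum 3.2416):

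- Read as 19 per parallel arm: difference/SD = 3.2416 × √(2/19) = 1.05.
- Read as 38 pairs: difference/SD of within-person differences = 3.2416/√38 = 0.53.

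It therefore gives no information about *r*.

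**Standard errors.** With *n* participants and a common SD of change:

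- true SE of the diet difference = SD × √(2(1 − *r*)/*n*)
- SE used by the independent t-test = SD × √(2/*n*)
- ratio, used to true = 1/√(1 − *r*)

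**Error rate and power, n = 38, balanced sequences, no period effect** (simulated, nominal 5%; power for a 0.5 SD difference):

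| assumed *r* | SE ratio | type I error, independent | type I error, paired | power, independent | power, paired |
|---|---|---|---|---|---|
| −0.5 | 0.82 | 11% | 5% | 57%* | 42% |
| −0.3 | 0.88 | 8.6% | 5% | 57%* | 47% |
| 0 | 1.00 | 5.1% | 5% | 58% | 57% |
| +0.3 | 1.20 | 2.0% | 5% | 59% | 72% |
| +0.5 | 1.41 | 0.6% | 5% | 60% | 85% |

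*Not a gain: it comes from the inflated type I error.

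**Which *r* might apply?** Each period has its own baseline, so a stable person effect cancels from both changes. Suppose the remaining visit noise is first-order autoregressive with monthly correlation ρ. Then

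- variance of each change ∝ 2(1 − ρ³)
- covariance of the two changes ∝ 2ρ⁴ − ρ − ρ⁷ = −ρ(1 − ρ³)²
- *r* = −ρ(1 − ρ³)/2

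This gives *r* = −0.22 at ρ = 0.5, −0.23 at 0.7, −0.12 at 0.9 and −0.07 at 0.95. The most negative value is about −0.24, near ρ = 0.63. True type I error is then about 5.7-7.7%, that is, 6-8%. Independent visit-to-visit measurement noise brings *r* closer to zero. A person-specific response to the shared Mediterranean diet would push it upward, possibly above zero.

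**Period.** With balanced sequences, leaving period out mainly costs precision. At *r* = +0.5 and an assumed period effect of 1 SD, power for 0.5 SD is 48% (independent), 58% (paired without period) and 85% (period-adjusted).

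**Within-diet tests.** Take two diets with the same true effect, each with about 50% power to show its own change, and treat the two tests as independent. The chance that exactly one is significant is 2 × 0.5 × 0.5 = 50%. That pattern is no evidence of a diet difference.

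**The case against.** The strongest defence is the general linear model for repeated measurements. It is a between-diet comparison, it can respect the pairing, and it is the only source of the confidence intervals that the section mentions. This stands in part. A reader might infer that the whole plan ignores the pairing, or that its confidence intervals are wrong; the text supports neither. The defect lies in the stated t-test and in the absence of any priority for the model over it.

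A second defence is that the independent t-test might be the standard two-sample cross-over test, which compares within-person period differences between the two sequence groups and is valid. The wording does not fit: the variable is defined as after minus baseline, which is the change itself, and sequence groups are not mentioned.

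A third is that the error may be small. That is fair: with a baseline in each period, *r* may lie near zero, where the test is close to nominal. The 11% and 0.6% error rates belong to assumed correlations of −0.5 and +0.5 and are not predictions for this trial.

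Two further inferences should not be drawn:

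- A reader might conclude that regression to the mean produces a calculable fall in LDL on each diet. But raised LDL is only one of four alternative lipid and glucose criteria, the document does not say that the T0 value is the qualifying one, and about half of each diet's changes start from T2.
- A reader might conclude that the diet contrast is biased by unequal sequences. But the article states 1:1 allocation with 25 per group and does not say that simple randomization is used. Bias would need imbalance among completers.

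In a condensed article, the lack of a named period term would not be a finding by itself.

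**Conclusion.** The point holds in this form: the plan explicitly states a between-diet test that assumes independent groups, in a design where the same people supply both sets of changes. The test is not valid in general. Its error is conservative with loss of power for positive *r*, anti-conservative for negative *r*, and negligible near zero. Since the document gives no *r*, neither size nor direction can be fixed; the figures above rest on assumed correlations, 38 completers, normal data and a two-sided 5% level. The within-diet paired tests do not address the trial's question whatever the correlation. The repeated-measurements model could supply a valid answer, but as written nothing makes it the deciding analysis. This should be corrected before analysis, because it concerns the primary result and, through the common approach, every secondary outcome.

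**What to change.** - Delete the independent-samples t-test on the per-subject changes.
- Declare one primary analysis: the within-participant difference between diets in LDL-cholesterol. Either of two forms will do: a mixed or repeated-measures model with diet, period and sequence as fixed effects and participant as a random effect, or the two-sample test of within-person period differences between the sequence groups. A properly specified version of the repeated-measurements model already planned would serve.
- Label the within-diet paired t-tests as descriptive.
- Apply the same model to the secondary outcomes.
- While editing, reconcile the statistical section, which calls the primary outcome change in body weight, with the abstract and the Outcomes section, which name LDL-cholesterol. This is a separate point.

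The cost is wording in the statistical section and possibly a different SPSS procedure. No extra visits, samples or participants are needed.
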